#### Selection of participants

Subjects participating in the study are recruited by the general practitioners involved. They introduce the study to patients who seem eligible and give interested patients a brochure about the trial, to be read at home. After having received consent, the general practitioners fax the name and telephone numbers of the interested patients to the research team. Subsequently the researcher calls the interested patients within one week. During this conversation the aim and implications of the study are explained again and the eligibility criteria are checked. Patients are eligible for participation when they meet the inclusion and exclusion criteria presented in Table 1.

If patients meet these criteria and wish to join the study, an informed consent form is signed before participation begins. The new participants receive another subacromial corticosteroid injection from the general practitioner for treatment of their first recurrence. If ineffective, this injection will be repeated within one month. Participants who have a recurrence of problems within one year after the last injection will contact their general practitioner, who will inform the researcher by fax. Subsequently the participant will be invited to visit the researcher at UMCG for a physical outcome measurement and to be randomized to one of the two treatment groups. Participants who do not have a recurrence within one year will not be randomized.

### Randomization

Participants will be block-randomized into two groups: surgery or usual medical care. Subsets of four participants are made per participating general practitioner. Two participants will be assigned to the treatment group and two to the control group. This process is repeated as the trial progresses. Block randomization is a method used to prevent unequal treatment-group sizes [27]. In this study, this method is used to ensure more or less equal treatment groups per general practitioner. It prevents participants referred by one single general practitioner from being all treated according to usual medical care or surgery.

Sealed, opaque envelopes in subsets of four per general practitioner are used for randomization. The envelopes look identical and have identification for the referring general practitioner as well as a sequential number for the subset. A random sequence of envelopes is generated by an independent person. The participants choose one envelope under supervision of the researcher.

### Interventions

The treatments the two study groups are assigned to are not different from those in usual medical care. The only difference is that the surgery group, in most cases, will have an operation after a shorter preoperative duration of symptoms compared to patients who fail to respond to conservative measures in usual medical care.

The operative treatment is an arthroscopic subacromial decompression performed within four weeks after randomization. Preoperatively no imaging will be performed, except for a shoulder radiograph. This is because the positive reactions to the previous injections have confirmed the SIS diagnosis. The operation is carried out in day surgery under general anesthesia, possibly extended with a regional nerve block for postoperative pain reduction. During the operation the patient is in a beach-chair position. The arthroscopy starts with an inspection of the glenohumeral joint, the intra-articular surface of the rotator cuff and the biceps tendon. Then the endoscope is introduced in the subacromial bursa. Subsequently the treatment consists of a bursectomy with partial resection of the anteroinferior part of the acromion and the coracoacromial ligament. If seen, tears of the rotator cuff will be noted but not repaired – the reason being that there is little evidence to either support or refute the efficacy of common interventions for rotator cuff tears [28]. Therefore, an ongoing discussion exists as to whether to operate on tears of the rotator cuff. As most rotator cuff tears are caused by degeneration, which is confirmed by histochemical and morphometrical research [29], an operation consisting of suturing degenerated tissue is not expected to be effective in the long term because of the ongoing process of postoperative degeneration and the associated risk of retears [30,31]. In this study, all participants have a painful arc syndrome and a positive impingement test. These patients can have a partial thickness rotator cuff tear, or in the worst case a small full-thickness rotator cuff tear. Any patients with a history and clinical symptoms of a massive rotator cuff tear (i.e. an inability to reach overhead, lift with an outstretched arm, and an impairment of pushing and pulling) will be excluded. As the outcome measures of this study focus on pain and functioning of the shoulder and not on the integrity of the rotator cuff, the extent of the damage, on the continuum from no tear to a small full-thickness tear, has no consequences for the study groups.

One senior surgeon ([name]) will undertake all procedures. Before discharge the participant receives a sling and instructions for daily pendulum exercises. Two weeks post-surgery the participant visits the clinic for wound inspection. New instructions will follow for home training exercises which focus on increasing the range of motion of the shoulder. Four weeks later the participant may start exercises for strengthening the rotator cuff muscles. If indicated, physiotherapy can be part of the rehabilitation process.

The group randomized to continuation of usual medical care will receive treatment prescribed by the general practitioner according to the Guidelines for Shoulder Problems of the Dutch College of General Practitioners [3]. In primary health care a broad spectrum of conservative treatments for subacromial impingement syndrome is available: rest, nonsteroidal anti-inflammatory drugs, corticosteroid injections, physiotherapy and manual therapy. If needed, the general practitioner can also refer the participant to a hospital of random choice for further assessment and/or to be evaluated for surgery.

### Outcome assessment

At inclusion (T_0_), at randomization (T_1_) and at three (T_2_), six (T_3_) and 12 months (T_4_) post-randomization, outcome assessment will take place in both study groups (Table 2). At all measurement points, outcome will be assessed by means of questionnaires which are sent to the participants by mail three days earlier. At T_1 _and T_4 _the participants are asked to visit the researcher at UMCG for an additional physical assessment. The questionnaires addressing those measurement moments can be filled in at home and be handed in at the patient's visit. The researcher checks all questionnaires for missing or incorrect data.

The outcome measures used focus on shoulder function, pain and health-related quality of life. They are disease-specific or generic, and from a patient- or physician-based perspective. The following applied measures are disease-specific and patient-based: the Shoulder Disability Questionnaire, the Shoulder Pain Score and the Shoulder Rating Questionnaire. The Individual Relative Constant Score is a disease-specific as well as a patient- and physician-based instrument. The Short-form 36 Health Survey and the Patient-perceived recovery are both generic and patient-based. For the cost effectiveness analysis a generic, patient-based questionnaire will be used. The specific characteristics of the outcome measures will be mentioned below.

#### Primary outcome measure

##### Shoulder Disability Questionnaire (SDQ)

The SDQ is a 16-item measure for functional status limitation in patients with shoulder disorders and assesses the past 24 hours [32]. The 16 questions can be answered with either yes, no or not applicable. The score is calculated by multiplying the yes/no ratio by 100.

#### Secondary outcome measures

##### The individual relative constant score

This shoulder assessment score is a modification of the Constant-Murley shoulder score, in which patient-reported subjective assessment and objective measurement of shoulder function takes place at a ratio of35:65 [33]. The system is divided into subjective measures for pain and daily activities and objective measures for range of motion (max. 75 points) and power (max. 25 points). The modified score contains the same items as the original score, but uses the functional performances of the uninjured collateral shoulder of the same individual as a reference [34]. It is expected to be more reliable for larger and incoherent patient populations because specific interindividual differences regarding the patient's age, gender and constitution as well as other individual physiological parameters are eliminated.

Shoulder strength measurement, which is a part of the Constant score, is performed according to a standard method, as proposed by Bankes et al. [35]. A digital dynamometer, the Handyscale^®^, is used and validated for this application [36]. It measures a maximum of 15 kilograms with two decimals and an interval of 20 grams. The test position is the subject standing with the arm in 90° elevation in the scapular plane, elbow extended and forearm pronated. An adjustable strap is placed around the forearm just proximal to the radiocarpal joint and attached to the Handyscale^®^. The dynamometer is firmly attached to a solid surface. The subjects are instructed to pull upward with maximum effort until requested to stop. The reading of the dynamometer is taken after five seconds of maximum effort. For both the uninjured and the affected arm, three successive maximum pulls will be obtained. The highest value out of these three provides the strength score for each arm. Patients unable to reach the test position will receive the value of zero. The scores for strength assessment in the Constant-Murley score range from zero to 25 pounds, hence to calculate the individual relative strength score the ratio of the maximum strength scores of the affected and the unaffected arm is multiplied by 25.

The scores for the other individual parameters range from zero to 75 points. To calculate the individual relative sum score for these items, the ratio of these scores for the affected and the unaffected arm will be multiplied by 75. The individual relative Constant score is calculated by adding the individual relative strength score and the individual relative sum score. The maximum attainable score is 100 points.

##### The Shoulder Pain Score (SPS)

The SPS is a questionnaire to assess pain experienced by patients with shoulder disorders and includes a 24-hour recall frame [37]. The score consists of six pain symptom questions and a 101-Numerical Rating Scale (NRS-101). The SPS has been proved to be a useful instrument for following the course of the disorder over time, and gives an indication when a patient feels cured. Each question receives a maximum of four points. The NRS-101 is also transposed to a four-point scale (0–9 = 1, 10–39 = 2, 40–69 = 3 and 70–100 = 4). The minimum SPS score is seven points, the maximum score 28.

##### Shoulder Rating Questionnaire (SRQ)

The SRQ is a self-administered patient-based instrument which assesses shoulder function in 19 multiple-choice questions covering seven domains [38,39]. Five subscales are graded separately by averaging the scores of the completed questions, multiplied by two and a weighting factor. The SRQ comprises two additional dimensions compared to the SDQ: recreational and athletic activities and work. The sum scores range from minimum 17 to maximum 100 points.

##### Short-form 36 Health Survey (SF-36)

The SF-36 is a generic health status measure. It is composed of 36 questions and standardized response choices, organized into eight multi-item scales: physical functioning, role limitations due to physical health problems, bodily pain, general health perceptions, vitality, social functioning, role limitations due to emotional problems, and general mental health [40,41]. For purposes of this study we used the standard version of the questionnaire, covering a four-week time frame. All raw scale scores are linearly converted to a zero-to-100 scale, with higher scores indicating higher levels of functioning or well-being.

##### Patient-perceived recovery (PPR)

In addition to the SF-36 there is the PPR, a one-item score concerning recovery following treatment, measured on a seven-point ordinal scale [42].

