**Methods/Design:**

The effectiveness of an arthroscopic subacromial decompression versus usual medical care will be evaluated in a randomized controlled trial (RCT). Patients are eligible for inclusion when experiencing a recurrence of SIS within one year after a first episode of SIS which was successfully treated with a subacromial corticosteroid injection. After inclusion they will receive injection treatment again by their general practitioner. When, after this treatment, there is a second recurrence within a year post-injection, the participants will be randomized to either an arthroscopic subacromial decompression (intervention group) or continuation of usual medical care (control group). The latter will be performed by a general practitioner according to the Dutch National Guidelines for Shoulder Problems. At inclusion, at randomization and three, six and 12 months post-randomization an outcome assessment will take place. The primary outcome measure is the patient-reported Shoulder Disability Questionnaire. The secondary outcome measures include both disease-specific and generic measures, and an economic evaluation. Treatment effects will be compared for all measurement points by using a GLM repeated measures analyses.

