### Study population

#### Sample size

The aim is to include 70 participants in the study. This number is based on the assumption that one year after randomization 50% of the participants will have recovered with conservative treatment [22,23] and 85% will successfully recover by means of arthroscopic subacromial decompression. The latter assumption is based on recovery rates presented in earlier studies in which successful results of arthroscopic subacromial decompression are reported in 86 to 95% of the cases [24-26]. A power analysis has been based on the effects of these treatments on shoulder function. In this study shoulder function will be measured with the Shoulder Disability Questionnaire, which is an outcome measure comparable to the instruments used in the referred articles. In order to detect a clinically relevant difference in shoulder function (35% differences in means) one year after randomization between the intervention and control group, 64 participants are needed – 32 in each group. These numbers are based on a power (1-B) of 0.80 and a significance level of 5% (two-sided). When a dropout rate of 10% is taken into account, 70 participants are to be included.

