### Statistical analyses

To estimate the effect of the interventions, analyses will be performed using SPSS 12.0 for the outcome measures. The baseline characteristics from both study groups will be compared for equality by means of an Independent Samples T-test (p-value 0.05) for continuous variables and a chi-square test for dichotomous variables. To compare treatment effects from measurement points T_0 _to T_4_, a GLM repeated measures analyses will be performed. Data will be analyzed according to the intention-to-treat principle and the per-protocol principle.

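### The T0–T4 repeated-measures GLM, the only treatment-effect analysis stated for the clinical outcomes, does not fit the Constant score (physical part measured at T1 and T4 only) or the ordinal recovery item

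*Protocol article*

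**What the plan says.** All references are to the Protocol article.

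- **Statistical analyses.** The section introduces its methods with "analyses will be performed using SPSS 12.0 for the outcome measures" and then gives the treatment-effect analysis: "To compare treatment effects from measurement points T_0 _to T_4_, a GLM repeated measures analyses will be performed". The abstract agrees: "Treatment effects will be compared for all measurement points by using a GLM repeated measures analyses". The only other tests named, a t-test and a chi-square test, are for comparing baseline characteristics.
- **Cost effectiveness.** The cost data go to a separate analysis by another office.
- **Outcome assessment.** Questionnaires are used at all five points: inclusion (T0), randomization (T1), and 3, 6 and 12 months later (T2, T3, T4). The physical examination is different: at T1 and T4 "the participants are asked to visit the researcher at UMCG for an additional physical assessment". The section refers to Table 2 for the schedule. That table is not in the text available for review.
- **The individual relative Constant score.** The total combines patient-reported items with measured range of motion and dynamometer strength, each expressed relative to the unaffected arm.
- **Patient-perceived recovery (PPR).** This is "a one-item score concerning recovery following treatment, measured on a seven-point ordinal scale".

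**The concern.** The stated model assumes that each outcome is measured at each of five visits, that its value means the same thing at each visit, and that means are a sensible summary. The Constant score fails the first condition by the protocol's own schedule. The PPR fails either the first or the second, depending on when it is asked, and the third is doubtful for a single ordinal item.

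Two things are at stake. First, the stated analysis cannot be carried out as written for the Constant score, so a substitute would have to be chosen later, possibly after the data are seen. Second, if the PPR has pre-randomization values and they enter the model, its group-by-time test would mix recovery after different treatments, and the result would not have a clear meaning.

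**Working it through.** **1. Scope of the stated analysis.** Six clinical measures are listed: the Shoulder Disability Questionnaire (SDQ, primary), Constant score, Shoulder Pain Score, Shoulder Rating Questionnaire, SF-36 and PPR. No treatment-effect analysis other than the T0–T4 GLM is named for any of them.

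**2. Constant score: schedule against model.**

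| | T0 | T1 | T2 | T3 | T4 |
|---|---|---|---|---|---|
| Questionnaires | yes | yes | yes | yes | yes |
| Physical examination | no | yes | no | no | yes |
| Complete Constant score | no | yes | no | no | yes |

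Even if the patient-reported items were collected at every point, the total could not be formed without range of motion and strength. Three of the five levels (T0, T2, T3) are empty by design. A classical repeated-measures GLM uses only participants with a value at every level, so the five-level form has no usable record.

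**3. What the two-level form does.** With T1 and T4 only, the group-by-time contrast is the between-group difference in mean (Y4 − Y1). Its F(1, n − 2) equals the square of the t statistic on change; with 64 participants this is F(1, 62). The analysis is valid. Its precision can be compared with ANCOVA of Y4 on Y1. Let σ1 and σ4 be the standard deviations at T1 and T4, and ρ their within-group correlation:

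- residual variance, change score: σ1² + σ4² − 2ρσ1σ4
- residual variance, ANCOVA: σ4²(1 − ρ²)
- difference: (σ1 − ρσ4)², which is never negative.

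If σ1 = σ4, the ratio of ANCOVA to change-score variance is (1 − ρ²) / [2(1 − ρ)] = (1 + ρ)/2. The article gives no ρ, so as an assumed range:

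| assumed ρ | (1 + ρ)/2 |
|---|---|
| 0.3 | 0.65 |
| 0.5 | 0.75 |
| 0.7 | 0.85 |

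ANCOVA costs one residual degree of freedom (61 instead of 62).

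**4. PPR: what a value would refer to at each point.** From the sections on the TRANSIT strategy and Selection of participants:

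- T0, inclusion at the first recurrence: the treatment already received is the first-episode injection.
- T1, randomization at the second recurrence: the treatment already received is the injection given after inclusion.
- T2 to T4: the allocated treatment.

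If the PPR is asked at all five points, its answers refer to three different treatment episodes. If it is not asked at T0 or T1, the T0–T4 model lacks those levels. The stated model is unsuitable in both cases.

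**5. PPR: the ordinal scale.** A GLM compares means and so treats the seven categories as equally spaced. To see whether this harms the test, a mean-based comparison at one time point was simulated with 32 per group, 20,000 replications, and two assumed skewed seven-category distributions. Type I error was 0.049 and 0.051 against a nominal 0.05. The difficulty is therefore one of scale and interpretation.

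**6. Is the PPR behind the sample size?** The Sample size section assumes that "one year after randomization 50% of the participants will have recovered with conservative treatment", against 85% with surgery. With two-sided 5% and 80% power, the two-proportion formula gives n = [1.960√(2 × 0.675 × 0.325) + 0.8416√(0.25 + 0.1275)]² / 0.35² = 26.9, so 27 per group, and 33 with continuity correction. The article states 32. Proportions thus come close to the stated number, but the same section says that the power analysis concerns shoulder function measured with the SDQ and does not mention the PPR.

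**The case against.** The strongest reply is that the analysis section is a short summary in a journal article and should be read sensibly: the named method would be applied at the visits where each outcome exists. On that reading, the Constant score gets a two-level GLM, which runs and is valid. An ordinal model or cut-off for one secondary item is ordinary detail for a full protocol or analysis plan, and its absence here is no fault. The PPR schedule lies in a table that cannot be seen. It can also be said that T0 and T1 precede allocation for every outcome, so nothing is special about the PPR.

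Much of this stands, and it rules out several stronger readings that a reader might infer:

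- *That the GLM is stated for every outcome.* It is not; costs are analysed separately.
- *That no repeated-measures GLM can be run on the Constant score.* Only the five-point form fails.
- *That the PPR is the outcome behind the stated power.* The Sample size section ties the power to the SDQ.
- *That comparing means of the ordinal item inflates type I error.* The simulation showed nothing of the kind.
- *That the PPR is known to lack pre-randomization values, or known to have them.* The available text does not settle this.

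Two parts of the reply do not stand. The article does not merely omit detail: it fixes the visits, T0 to T4, and the abstract repeats that all measurement points are used, which conflicts with its own schedule for the Constant score. And the PPR does differ from the other measures. A pre-randomization SDQ or pain score describes the participant's current state and can serve as a baseline; an answer about recovery after an earlier injection cannot.

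**Conclusion.** The point holds in a limited form. The stated T0–T4 repeated-measures GLM does not match the protocol's schedule for the Constant score and is unsuitable for the PPR whichever way that item is scheduled. Two of the six clinical measures are affected, both secondary; the SDQ fits the stated visits. The consequence is an analysis that cannot be followed literally for one measure and would be hard to interpret for the other, plus some loss of precision if the Constant score falls back on a change-score test. With an assumed T1–T4 correlation of 0.3 to 0.7 and equal variances, ANCOVA would have 65% to 85% of that test's residual variance. Severity is low to moderate.

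The conclusion assumes that the physical part of the Constant score is measured only at the two visits named in the text, and that the GLM is the classical form requiring complete records. For the PPR it does not depend on the unseen Table 2, because both possible schedules lead to the same recommendation.

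**What to change.** Amend the statistical analyses section as follows:

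1. Limit the longitudinal model to outcomes measured at every visit the model includes.
2. Analyse the Constant score at T4 by ANCOVA, adjusted for its T1 value.
3. Compare the PPR at post-randomization visits only, with T4 as the main time point, by an ordinal or rank method (proportional-odds regression or a Mann-Whitney test). If a proportion recovered is also to be reported, fix the cut-off in advance.
4. Align the abstract's sentence on all measurement points with these changes.

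The cost is a few sentences. No new data, visits or participants are needed, since the T1 and T4 Constant scores are already scheduled.
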